### Participant timelines

Outcome measures are collected at pretreatment (T1), post-treatment (T2) and, in the case of those participants allocated to Arm A or Arm B, also at 6 months post-treatment (T3). A time schedule of enrolment, interventions and measures is presented in Table 1.

**Table 1 T1:** Enrolment, interventions and assessments

**Contact and home visits**	**Screening or diagnostic interview**	**Consent and TENALEA allocation**	**Pretreatment (T1) visit**	**Induction visit by therapist**	**Intervention: a-NFPP (home) IY (local hall)**	**Post-treatment (T2) visit (TAU = end of study)**	**6 month follow-up (T3) visit (a-NFPP/IY = end of study)**
**Timeline**	Week 1 to Week 10			Week 11 to 12	Week 13 to 24	Week 25 to 28	Week 50
**Enrolment**							
Participant informed consent	✓	✓					
**Eligibility**							
WWP (child hyperactivity); parent-completed scale	✓						
PIP developmental scales; research-fellow-administered scale	✓						
DISC-IV ADHD scale, child; research-fellow-administered interview	✓						
**TENALEA allocation**			✓				
**Interventions**							
Arm A: a-NFPP	✓	✓	✓	✓	✓	✓	✓
Arm B: IY	✓	✓	✓	✓	✓	✓	✓
Arm C: TAU	✓	✓	✓			✓	
**Measures**							
**Primary outcome**							
SNAP IV-P ADHD scale; parent-completed questionnaire			✓			✓	✓
**Secondary outcomes**			✓			✓	✓
Child’s solo play; observation measure, research-fellow-completed			✓			✓	✓
SNAP IV-T ADHD scale; teacher-completed questionnaire			✓			✓	✓
SNAP IV-P and T ODD scale: parent- and teacher-completed questionnaires			✓			✓	✓
ECBI (ODD measure); parent-completed questionnaire			✓			✓	✓
CSRI-Revised (economic costs); research-fellow-administered questionnaire			✓			✓	✓
EQ-5D QOL: Parent and parent proxy; parent-completed questionnaires			✓			✓	✓
**Mediators**							
FMSS (maternal expressed emotion); research-fellow-rated			✓			✓	✓
GIPCI, child/parent observation measure; research-fellow-rated			✓			✓	✓
Cookie delay task, child observation measure; research-fellow-rated			✓			✓	✓
GHQ - maternal; parent-completed questionnaire			✓			✓	✓
**Moderators**							
CSS (parental ADHD); parent-completed questionnaire			✓				
Preschool ADHD Risk Index; research-fellow-scored index			✓				
EASI (child temperament); parent-completed questionnaire			✓				
Demographic questionnaire; parent-completed questionnaire			✓				
Genetic testing (saliva sample); self-collected, parent & child						✓	✓
LOT; research-fellow-rated							✓
WAI-S; parent- and therapist-completed questionnaires			✓			✓	
FSI; parent- and therapist-rated			✓			✓	

a-NFPP: adapted New Forest Parenting Programme; CSRI-R: Revised Client Service Receipt Inventory; CSS, Current Symptoms Scale; DISC-IV, Diagnostic Interview Schedule for Children Version 4; EASI, Emotionality, Activity, Sociability and Impulsivity; EE, expressed emotion; ECBI, Eyberg Child Behaviour Inventory; EQ-5D, EuroQol - 5 Dimensions; FMSS, five-minute speech sample; FSI, Family Strain Index; GHQ, General Health Questionnaire; GIPCI, Global Impressions of Parent–child Interactions; IY, Incredible Years; ODD, oppositional defiant disorder; PARI, Preschool ADHD Risk Index; PIP, Parenting Intervention Project; SNAP-IV-P, Swanson, Nolan and Pelham Version 4 parent version; SNAP-IV-T, Swanson, Nolan and Pelham Version 4 teacher version; TAU, treatment as usual; WAI-S, Working Alliance Inventory, Short Form; WWP, Werry-Weiss-Peters Activity Rating Scale.

### Sample size

The trial is powered for two comparisons of interest.

Primary question: adapted-NFPP versus Incredible Years (Arm A vs Arm B).

Is adapted-NFPP superior to IY in terms of reductions in parent-rated ADHD symptoms? Assuming a conservative estimate of effect size difference of 0.4 standard deviation between adapted-NFPP and IY, an intraclass correlation of 0.08 for parents treated in the same IY groups and a drop-out rate of 10% (considerably higher than in the original trials) it is estimated that 141 individuals will be needed per treatment arm to provide sufficient power to test the hypothesis that the adapted-NFPP is superior to IY in terms of reduction in ADHD symptoms (total *N* = 282). This equates to a difference of mean 0.28 and standard deviation 0.7 on the SNAP-IV-P ADHD rating scale (the primary outcome) using a 5% two-tailed test of significance and 80% power. A design effect of 1.28 has been calculated from the formula:

$$1+\left(m-1\right)p$$

in the CONSORT (Consolidated Standards of Reporting Trials) statement for nonpharmacological interventions [66].

Secondary question: adapted-NFPP versus treatment as usual (Arm A vs Arm C).

Is the adapted-NFPP superior to TAU in terms of reductions in parent-rated ADHD symptoms? Again assuming a conservative estimate of effect size difference between adapted-NFPP vs TAU, a group of 141 adapted-NFPP and 47 TAU will give 81% power to detect an effect size of 0.5 on the SNAP-IV-P ADHD score (equating to a difference of mean 0.35 and standard deviation 0.7) with 5% two-tailed significance. No intraclass correlation has been applied for this calculation, as both adapted-NFPP and TAU will be delivered individually.

On this basis, each of the three centres will recruit approximately 110 families with a preschool-aged child (age 2 years 9 months to 4 years 6 months) with high levels of ADHD symptoms (total *n* = 329) into the trial. Families will be randomized with intention to treat to either (i) adapted-NFPP as an individually delivered, home-based parenting programme (*n* =141, leaving 127 for final analysis with 10% drop-out); (ii) IY delivered in groups of eight (*n* = 141, leaving 127 for final analysis with 10% drop-out); or (iii) TAU (*n* = 47, leaving 42 for the final analysis with 10% drop-out).

### Recruitment

The plan for recruitment takes into account that (a) two research fellows will be available at each centre to conduct screening and the diagnostic interview, recruit participants to the study and complete T1 to T3 visits for each tranche and (b) two pairs of therapists will be employed at each centre to cover the two parenting programmes. Given a target recruitment of *n* = 329 participants (110 participants per centre) and factoring in school holiday periods, it is estimated that five or six parenting programme tranches will be needed, with 18 to 22 parents enlisted per tranche across centres. An allocation ratio of 3:3:1 will mean that approximately eight parents will be allocated to each pair of therapists. Two NFPP therapists will each work on a one-to-one basis with four parents over the 12-week period of the programme and two IY therapists or leaders will conduct a group-based programme in a local hall with eight parents, whose partners may also attend the group.

The collaboration of local agencies and services acting as participant identification centres across each of the sites will be sought to help achieve recruitment targets for each tranche of parenting programmes. Practitioners and clinicians across agencies will make study enlistment packs available to parents. These packs contain a letter to the parent, an information sheet, an expression of interest form, a consent to screen form and a freepost envelope for the return of the expression of interest and consent forms to the research office. Posters, radio advertisements and social media will also be used to recruit a broad range of parents to the study. For the purpose of ensuring sufficient numbers of hard-to-reach and potentially difficult-to-treat families, the sample will be enriched by targeting a range of different referral sources and using previously developed outreach strategies to increase engagement of these families. Multiple recruitment routes will be used at each of the centres participating in the trial; these will include health visiting and Sure Start professionals; speech and language clinics; community paediatric clinics; and CAMHS. To determine the proportion of ‘hard-to-reach’ and potentially treatment-resistant families participating in the trial, the sample will be characterized using a number of factors that have been associated with such families. These factors will include: socioeconomic status; education; employment; number and age of siblings residing in the home; ethnicity; single parent status; age of parent at time of birth; parental mental health problems or ADHD; child language and communication problems and the presence of other child comorbid conditions.

## Informed consent

In the 10-week period prior to the start of each parenting programme tranche, two research fellows in each area will have responsibility for obtaining written informed consent to administer screening and diagnostic measures to parents, usually at their homes or some other convenient location or, if necessary, by phone. Standard informed consent procedures will be followed both for the administration of screen and diagnostic interview measures and, if the parent is eligible and willing, for participation in the full study. If the parent is not eligible, the parent will be informed and this will be confirmed in writing to the parent and the parent’s clinician or practitioner where appropriate. If the measures indicate that (1) all inclusion criteria have been met and (2) that in the event of being allocated to IY, the parent would be available to attend an IY programme on a fixed day in a local centre or hall where crèche facilities will be made available, the parent and child will be eligible for inclusion in the full study. A screen and diagnostic interview case report form (CRF) will be completed by the research fellow, indicating that all inclusion criteria were met together with the parent or main caregiver scores for all completed measures.

If the parent is willing to participate, the research fellow will arrange to visit the parent’s home. At the T1 visit, written informed consent to participate in the full study will be obtained and T1 measures will be collected. Protocol assessments will be performed according to the schedule in Table 1. After consent is obtained and the visit has been completed, a T1 CRF will be completed by the research fellow to record the measures completed at the visit and the scores for these measures.

The research administrator will then liaise with the UoSCTU to complete the process of randomization and the participant will be randomized to an arm of the study. General practitioners will be informed of the parent’s participation both at the start and end of the study. All participants will be informed that they can withdraw from the study at any time without their rights being affected. In the case where consent to treatment is withdrawn but the participant agrees to remain in the research study, the participant will be followed to completion.

### Allocation and blinding

After consent has been received, the participant will be randomized into an arm of the study by the UoSCTU using the online TENALEA system [67]. Randomization procedures will be carried out prior to the start of each parenting programme tranche and will take place during normal working hours (Monday to Friday, 9 a.m. to 5 p.m.). Only the trial co-ordinator (DMC) and designated research administrator staff at each centre will be responsible for liaising with the UoSCTU in randomizing participants. When possible and to help maintain blindness, groups of eight or more participants within each centre will be randomized together. Upon receipt of an electronic file from each centre, designed by the UoSCTU to provide participant IDs and initials, centre attended and other details necessary for TENALEA system randomization, the UoSCTU will carry out randomization. Parents will be block randomized to adapted-NFPP, IY or TAU arms in the ratio 3:3:1. Automated email confirmation of randomization will be sent to the authorized individual at each centre. Details of the randomization will then be added to the screen and diagnostic interview CRF by the research administrator. A copy of this CRF, together with the T1 CRF, will be checked and verified by the centre principal investigator and sent by courier or, in the case of the Southampton centre, delivered by hand to the UoSCTU, along with a copy of all measures collected at these two visits. Data measures will be gathered and CRFs completed and processed in a similar manner at T2 and T3 visits.

Participants in each centre will be informed by designated research staff as to which arm of the study they have been allocated and this will be confirmed in writing. In the case of parents randomized to the TAU group, parents will be offered a place on a parenting programme in the community to commence approximately 4 weeks after T2 data collection, which will be ‘end of study’ for TAU participants. Those participants allocated to adapted-NFPP and IY will also be asked to complete T3 measures 6 months after treatment. Research fellows will remain blind to treatment allocation. Research fellows will inform the participant when arranging home visits at T2 and T3 data collection that this blindness should be maintained on their visit. Any breaches of blindness will be recorded. The screen and diagnostic interview CRF containing allocation details will be filed separately from other documents contained in participant files to which the research fellows will have access, as will all other such documents.

### Data collection methods

Data collection will take place at the parent’s home at each of the three time points. All research fellows will have a degree in psychology and will be trained in the administration of all measures. The majority of measures are self-completed (on paper) by the parent, as indicated in Table 1. A description of study instruments are outlined below together with details of reliability and validity, where available.

#### Screen and diagnostic interview

##### Werry-Weiss-Peters activity rating scale (WWP: [45])

The WWP is a 27-item parent-completed questionnaire measuring hyperactivity. This has been shown to identify the top 15 to 18% of the population using a score of 20 as a cut-off [68]. Psychometric properties have been reviewed by Barkley [69], who reported discrimination between hyperactive and normally developing children to be good. The interparent agreement has also been found to be good (*r* = 0.82) [70]. The WWP is easy to complete and has been shown to have high levels of internal consistency, to correlate with other measures of hyperactivity and to identify children who have activity problems 5 years later [71].

##### Diagnostic interview schedule for children – version 4 (DISC-IV - ADHD Scale [46])

If a score of 20 or more is reported on the WWP, the DISC-IV will be administered to the parent or main caregiver. The DISC-IV uses criteria contained in the DSM-IV and enquires about hyperactive and inattentive symptoms and impairment in both home and school settings. The standard DISC-IV impairment algorithm requires moderate impairment in at least one area of functioning related to ADHD symptoms, as judged by parental responses. Impairment on the DISC is defined by the degree to which the symptoms have (a) caused distress to the child; (b) affected relations with caregivers, family, friends or teachers; or (c) affected school functioning. The DISC has been shown to have moderate to substantial test-retest reliability and internal consistencies. Training in administration and scoring of this measure was overseen by the clinical lead (MT), the trial co-ordinator and other researchers with extensive experience in its administration.

##### Parent Involvement Project (PIP) developmental scales [47]

If DISC-IV inclusion criteria are met, the PIP developmental scales will be administered by the research fellow. This developmental checklist is widely used by educational psychologists as either an interview schedule with the parents or an observation schedule. It gives a profile of the child in five different areas: physical development, social development, eye-hand co-ordination development, development of play and language development. The chart also suggests the age that children will normally develop these skills and has age norms up to age 4 years. In this study, it will be used as an interview schedule with the mother and it will give an indication of any possible developmental delay. An educational psychologist was consulted regarding the scoring of these scales and training in the administration of this measure by the research fellow was carried out by the clinical lead (MT).

#### Outcome measures

##### SNAP-IV parent (SNAP-IV-P: 56]) and teacher scales (SNAP-IV-T: 56])

The self-completed SNAP-IV-Parent ADHD Scale is the primary outcome measure in this trial with the teacher-completed SNAP-IV-T ADHD Scale and the SNAP-IV-P and T ODD Scale used as secondary outcome measures. The Multimodal Treatment Study of Children with ADHD (MTA) version of the SNAP-IV is used in this trial [72]. The 26 items include 18 ADHD symptoms (nine inattentive, nine hyperactive or impulsive) and 8 ODD symptoms, as specified in the DSM-IV. Items are rated for frequency by the parent or teacher on a 4-point scale (0 = not at all to 3 = very much) and average ratings per item are then calculated for each subscale. Bussing et al. [56] examined the psychometric properties of the SNAP-IV-P and found that the internal consistency for overall parent ratings was 0.94 (inattentive 0.90; hyperactive or impulsive 0.79, ODD 0.89). Internal consistency for the SNAP-IV-T was 0.97 (inattentive 0.96, hyperactive or impulsive 0.92, ODD 0.96). Interrater reliability between parent and teacher ratings was 0.49 for inattention, 0.43 for hyperactivity or impulsivity and 0.47 for ODD and all were statistically significant (*P* < 0.001).

##### Eyberg child behaviour inventory (ECBI: [57])

The ECBI is a parent-completed 36-item inventory for the assessment of problem behaviours in children aged 2 to 16 years. It includes a seven-point intensity scale (never to always) that measures the frequency of each problem behaviour and a yes-no problem scale that identifies whether the behaviour is currently seen as a problem. The ECBI can be used both as a clinical screening measure for identifying and treating externalizing problems in children and as a measure of treatment outcome. Cut-offs representing high-risk children are 127 for the problem scale and 11 for the intensity scale. The ECBI has been shown to correlate well with independent observations of children’s behaviours and can differentiate between clinic-referred and nonclinical populations. Reliability coefficients for the ECBI scales range from 0.86 (test-retest) to 0.98 (internal consistency) [57,73].

##### Child’s solo play [27]

This independent observation measure, which is carried out by the research fellow during 5 minutes of solo child play with a standard activity toy, is an important secondary outcome measure. The ‘Little People Animal Sounds Zoo’ is a multipurpose toy that includes a number of different activity zones (for example, water slides, a ticket office and a tree cave). Patterns of attending to and switching from one activity to another during independent play are measured and an index of attention or engagement is calculated (time on task divided by total number of switches from zone to zone). High index scores represent more attention and less switching. This measure has high test-retest reliability (Pearson *r* = 0.81) and interrater reliability (Pearson *r* = 0.76) and good validity, differentiating, as it does, children with ADHD from those without. Research fellows are trained in the administration and scoring of solo play by one of the principal investigators (DD), who has extensive experience in the development and scoring of this measure.

##### Revised client service receipt inventory (CSRI-R: 58])

The CSRI-R allows the collection and combining of health economic data in a retrospective format from a range of different sources using a range of different approaches (interview, health records, and so on). In this study, a 3-month recall window or ‘since the last CSRI’ will be used for the interview section. The interview section conducted by the research fellow asks about the parental background and whether the child’s behaviour has affected career prospects and has had an impact on the finances of the family. There is also a section on use of services, including any major service use at any point in the young person’s life. The CSRI has good face validity [58] and test-retest reliability and has been used in several evaluations of care for children with needs related to mental health. Instruction in the completion of this measure will be given by experienced health economists.

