#### Resource use and family borne costs

Detailed information on all resources required to provide both the adapted-NFPP and the IY programme will be collected. This will include the design of a time collection form to record therapist time spent providing the intervention inclusive of preparation and travel time. It will also include resources such as manuals and handouts, training and supervision and any necessary fidelity procedures. Resource use will be combined with relevant unit cost data to provide estimates of the costs of providing these interventions. The detailed breakdown of the types of costs required will allow carrying out sensitivity analysis of the effect of varying any aspect of how the interventions are provided. It will also allow comparison of the economics of different modes of provision.

Patient-reported resource-use measures are an important component and one of the most challenging parts of an economic evaluation. The CSRI [58] is considered one of few resource-use measures that have been comprehensively tested and the validity and reliability of the instrument is considered good, with consistency generally fairly well demonstrated [81]. An adapted version of the CSRI will be used to collect detailed information from all parents indicating contacts with frontline professionals or specialized services and will allow identification of ADHD related health and social care resource use required by individuals and families. This will include costs related to counselling services and support groups, child education and day care, as well as employment related costs due to child’s health/behaviour. There is no doubt that there is a tension between demand for information on costs and its supply; this comprehensive cost data collection will provide the opportunity to report on economic implications of ADHD in preschool children.

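### At T2, research fellows who must stay blind also take the CSRI-R service-use interview, which puts the blinding of the observer-rated measures at risk

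*Protocol article*

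**What the plan says.** Under Allocation and blinding: "Research fellows will remain blind to treatment allocation". The stated supports are that parents are asked, when T2 and T3 visits are arranged, to preserve that blindness; that breaches are recorded; and that papers showing allocation are filed apart.

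The CSRI-R falls to the same role. Table 1 lists "CSRI-Revised (economic costs); research-fellow-administered questionnaire" at T1, T2 and T3. The CSRI-R section says "The interview section conducted by the research fellow asks about the parental background" and continues: "There is also a section on use of services, including any major service use at any point in the young person’s life". On timing, "a 3-month recall window or ‘since the last CSRI’ will be used for the interview section". Under Resource use and family borne costs, the instrument is to "collect detailed information from all parents indicating contacts with frontline professionals or specialized services", and the costs listed there include counselling and support groups. Therapist time spent delivering the programmes is recorded on a separate form.

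Fellows also make the observations. Solo Play is a measure "which is carried out by the research fellow during 5 minutes of solo child play", and Table 1 marks Cookie Delay, GIPCI and FMSS as rated by research fellows at T1, T2 and T3. On staffing, the Recruitment section says "two research fellows will be available at each centre", and these fellows complete the T1 to T3 visits.

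**The concern.** Two instructions pull against each other. The parent is asked not to let the fellow learn the arm, and the same role then asks that parent which professionals and services the family has used. The arms differ in just this respect: weekly home visits by a therapist (adapted-NFPP), a weekly group in a local hall (IY), or neither (TAU). The therapists are nurses, psychologists, family support workers and social workers, the kind of contact a service-use interview asks about. A full answer can point to the arm; a guarded one weakens the cost data.

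What is at stake is the observer-rated evidence. The primary outcome is completed by a parent who knows the arm. Solo Play is the only clinical secondary outcome rated by a research fellow, and the Discussion relies on direct observation to separate rater effects from setting effects. GIPCI, FMSS and Cookie Delay serve the exploratory mediation question. All of these are worth more if the rater does not know the arm.

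**Working it through.** The plan gives no figure on this point to reproduce. Two checks apply: how much of the programme the interview covers, and which measures are exposed.

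**1. Overlap of the recall window with the programme**

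Inputs from Table 1: programme in weeks 13 to 24 (12 weeks); T1 within weeks 1 to 10; T2 in weeks 25 to 28; T3 in week 50. The recall window is three months or back to the previous CSRI. Assumption: three months is 13 weeks, counting the visit week.

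For a visit in week V, the three-month window is weeks V − 12 to V. The overlap is the number of those weeks that fall in 13 to 24.

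- T2 in week 25: window 13 to 25; overlap weeks 13 to 24 = 24 − 13 + 1 = **12 of 12**.
- T2 in week 28: window 16 to 28; overlap weeks 16 to 24 = 24 − 16 + 1 = **9 of 12**.
- T2, counting from the previous CSRI (T1, week 10 at the latest): **12 of 12**.
- T3 in week 50, three months: window 38 to 50; overlap **0 of 12**.
- T3, counting from the previous CSRI: window starts in week 26 or 29; overlap **0 of 12**.

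The direct exposure is therefore at T2. At T3 two routes remain: a fellow who learnt the arm at T2 may remember it, and the item on major service use over the child's lifetime has no window. A T3 visit does show that the family is not in TAU, because TAU has no T3, but that has nothing to do with the CSRI-R.

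**2. Which measures are exposed**

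| Measure | Use in the trial | Rated by | Exposed by this route? |
|---|---|---|---|
| SNAP-IV-P ADHD | Primary | Parent | No |
| SNAP-IV-P ODD, ECBI | Secondary | Parent | No |
| SNAP-IV-T | Secondary | Teacher | No |
| Solo Play | Secondary | Research fellow | Yes, if scored after the interview |
| Cookie Delay | Mediator | Research fellow | Yes, if scored after the interview |
| GIPCI | Mediator | Research fellow, later from video | Yes, if the coder has heard the interview |
| FMSS | Mediator | Research fellow, speech taped | Yes, if the coder has heard the interview; the speech itself may also disclose |

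**3. Whether the stated safeguards close the gap**

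Separate filing stops a fellow reading the allocation; it does not stop a parent stating it. Recording a breach documents it but does not restore the rating. The request to parents is the only safeguard that acts during the visit, and it conflicts with the interview's purpose. The therapist time form means the costing of delivery does not depend on parents listing sessions, but the article does not say that parents are told to leave them out.

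**The case against.** The strongest reply is that disclosure is inferred. The article does not say that the CSRI-R asks about the trial programmes, and their delivery is costed from another source. A reported support group or health-visitor contact may also have nothing to do with the trial. This stands: a reader might infer that the visit itself reveals the arm and that the observed outcomes lose their protection, but the documents support a risk and no more. If the live tasks come before the interview, their T2 scores are protected.

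A reader might also infer that the visiting fellow knows the arm when coding the recordings. The article says only that a research fellow rates them; with two fellows per centre, coding by the other one fits the text. Nor do T2 and T3 carry equal risk, as the windows show.

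A reader might want a bias in standard deviations. The documents give neither the share of fellows unblinded nor the shift in a rating. The 0.4 SD planning difference belongs to the parent-rated SNAP-IV-P, which this route cannot touch, so it is no yardstick. For adapted-NFPP against IY, an equal shift in both arms would cancel; bias there needs a fellow who favours one programme. That cancellation does not help against TAU.

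Finally, visit order and coder assignment are details an article may leave to the full protocol or a manual. That is fair as to order alone. But the article does state that the blinded role conducts the interview, and the safeguards it states do not address that assignment. Central handling of allocation and randomization in batches deserve credit, but they do not act on what a parent says at the visit.

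**Conclusion.** The point holds as a risk to assessor blinding, chiefly at T2. The interview window there covers 9 to 12 of the 12 programme weeks, assuming three months is 13 weeks and the visits follow Table 1. The reach is one fellow-rated clinical secondary outcome (Solo Play) and three observed mediators (Cookie Delay, GIPCI, FMSS). At T3 the risk is limited to carry-over from T2 or the lifetime service item. The parent-rated primary outcome, the teacher ratings and the sample size are unaffected. The size of any bias cannot be derived from the documents. The change is worth making because a stated role assignment works against a stated blinding property and the remedy is cheap.

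**What to change.** 1. At T2 and T3, complete and score Solo Play and Cookie Delay, and record GIPCI and FMSS, before the CSRI-R begins.
2. Have the GIPCI and FMSS recordings coded by the centre's other research fellow, who did not make the visit. The plan already provides two per centre.
3. Tell parents not to report trial-programme sessions in the CSRI-R, including under the lifetime item, since therapist delivery time is already captured on its own form. This step also limits carry-over to T3, which visit order alone cannot do.

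The cost is a less flexible visit order and some logistics for exchanging recordings. What remains is that a parent's free speech in the FMSS may still reveal the arm to whoever codes it, and a parent may disclose despite the instruction. Recording of breaches should therefore continue.
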